## Abstract

**Background:**

Targeted deprescribing of anticholinergic and sedative medications in older people may improve their health outcomes. This trial will determine if pharmacist-led reviews lead to general practitioners deprescribing anticholinergic and sedative medications in older people living in the community.

**Methods and analysis:**

The standard protocol items: Recommendations for Interventional Trials (SPIRIT) checklist was used to develop and report the protocol. The trial will involve older adults stratified by frailty (low, medium, and high). This will be a pragmatic two-arm randomized controlled trial to test general practitioner uptake of pharmacist recommendations to deprescribe anticholinergic and sedative medications that are causing adverse side effects in patients.

**Study population:**

Community-dwelling frail adults, 65 years or older, living in the Canterbury region of New Zealand, seeking publicly funded home support services or admission to aged residential care and taking at least one anticholinergic or sedative medication regularly.

**Intervention:**

New Zealand registered pharmacists using peer-reviewed deprescribing guidelines will visit participants at home in the community, review their medications, and recommend anticholinergic and sedative medications that could be deprescribed to the participant’s general practitioner. The total use of anticholinergic and sedative medications will be quantified using the Drug Burden Index (DBI).

**Outcomes:**

The primary outcome will be the change in total DBI between baseline and 6-month follow-up. Secondary outcomes will include entry into aged residential care, prolonged hospitalization, and death.

**Data collection points:**

Data will be collected at the time of interRAI assessments (T0), at the time of the baseline review (T1), at 6 months following the baseline review (T2), and at the end of the study period, or end of study participation for participants admitted into aged residential care, or who died (T3).

**Ethics and dissemination:**

Ethical approval has been obtained from the Human, Disability and Ethics Committee: ethical number (17CEN265).

**Trial registration:**

ClinicalTrials.gov ACTRN12618000729224. Registered on May 2, 2018, with the Australian New Zealand Clinical Trials Registry

**Supplementary Information:**

The online version contains supplementary material available at 10.1186/s13063-021-05711-w.

## Background

Polypharmacy, the use of five or more of medications, is prevalent amongst older adults positioning them at a higher risk of drug-drug interactions and one or more inappropriate medications. Inappropriate medications are defined as those whose potential harm outweighs their possible benefits currently in the individual [1]. Deprescribing, the process of safely reducing or discontinuing unnecessary or harmful medicines with clinical supervision, can decrease polypharmacy, reduce inappropriate medicine use, and may improve health outcomes [2].

Disease-specific guidelines offer little advice regarding deprescribing potentially harmful medications [3, 4] for people with multimorbidity. Of note, anticholinergic and sedative medications can be inappropriately prescribed for older adults [5]. The cumulative, long-term use of these medications is associated with several negative health consequences, including impaired muscle strength, worsening cognition, increased frailty, poorer physical functioning (e.g., balance), heightened risk of falls, increased rate of hospitalizations, entry into residential care, and even death [6, 7]. Polypharmacy is associated with frailty [8], a geriatric syndrome present in many older adults. Frailty increases with age due to age-related physiological deterioration. Up to half of the people aged over 85 years experience frailty [2]. Small trigger events, like a seasonal illness or fall, can cause a sudden decline in health and negative outcomes in already frail individuals [2, 9, 10]. Little is known on how a quantified measure of frailty could inform and help in targeting frail individuals for deprescribing.

Deprescribing of unnecessary anticholinergic and sedative medications has been shown to potentially improve health outcomes of older people [2, 9], including cognition [10], and reducing the risk of falls [11] and hip fractures. In addition, although inconclusive to date, evidence suggests that deprescribing could improve reported quality of life [12, 13].

Although previous studies have demonstrated the feasibility and overall safety of deprescribing, questions remain regarding how best to do it in practice [14, 15]. In a multi-disciplinary residential aged care setting, pharmacist-led interventions have successfully reduced unnecessary prescribing of sedative and anticholinergic medications [16, 17]. A cluster randomized controlled trial of clinical decision support software targeting deprescribing anticholinergic and sedative medications for pharmacists conducting the Home Medicines Review in Australia increased pharmacists’ recommendations to reduce anticholinergic and sedative medications but not their uptake [18].

The drug burden index (DBI) is a linear, additive pharmacological model that uses pharmacokinetic and pharmacodynamic principles to calculate an individual’s total exposure to anticholinergic and sedative medications [14]. Exposure to each additional unit of DBI has been shown to have a negative effect on the physical function of older people, equivalent to three additional physical comorbidities [14]. An association between increasing DBI and impaired function has been demonstrated in a cross-sectional analysis of two populations of older people in the USA [19], in older Australian men [20], and a longitudinal study of community-dwelling older people in the USA [21]. Furthermore, increasing DBI is associated with prevalent and incident frailty [22] and frailty transitions [23].

In this randomized controlled trial in a community setting, we will test a targeted approach to pharmacist-led deprescribing of medications contributing to DBI in frail older adults. Specifically, this study will test the utility of a frailty measure for targeting deprescribing on individuals with the greatest potential for improvement. We will identify older adults seeking funded care support who undergo a structured, comprehensive need assessment, develop a frailty measure using data obtained through these assessments, and stratify our participants into three groups based on their frailty index. Pharmacists will visit participants in their homes, record current medication use, and develop recommendations for deprescribing, which are passed to the patient’s primary physician for consideration. We will measure changes in DBI medication use and differences in hospitalization and entry into aged residential care.

## Methods

### Hypotheses and aims

We hypothesize that implementing a pharmacist-led medication review and provision of deprescribing recommendations to general practitioners (GP) will reduce the use of anticholinergic and sedative medications in community-dwelling older people compared to the control arm overall and that the reduction will be more pronounced for older people with a greater level of frailty. Thus, the primary objective is to determine if pharmacist-led medication reviews focused on reducing anticholinergic and sedative medications lead to GPs deprescribing these medications for older people living in the community. The secondary objective is to determine if a frailty measure based on data collected in the interRAI Home Care [24] and Contact assessment [25] can identify a group of older people who could benefit the most from deprescribing.

The interRAI is a comprehensive assessment database system utilized internationally and in New Zealand to standardize the evaluation of complex care needs of older people. It is routinely used to collect data regarding patients’ medical and functional status [26]. In New Zealand, the comprehensive Home Care assessment [24] is used for persons seeking admission into publicly funded aged residential care, while the shorter contact assessment [25] is for home-based support services. The reliability of the interRAI™ has been tested, and it has been shown to meet or exceed the standard cut-offs for acceptable reliability [27].

### Study design

This will be a pragmatic two-arm randomized controlled superiority trial to test general practitioner uptake of pharmacist recommendations to deprescribe anticholinergic and sedative medications that are causing adverse side effects in patients. The cumulative use of anticholinergic and sedative medications listed in Table 1 for each participant will be quantified using the DBI [14]. New Zealand registered pharmacists will use previously pilot-tested deprescribing guidelines to recommend to GPs sedative and anticholinergic medications with a potential to be deprescribed [28, 29].

**Table 1 Tab1:** Anticholinergic and sedative medications

Generic medicine name	ATC code	Generic medicine name	ATC code
Alprazolam	N05BA12	Methyldopa	C02AB01
Amitriptyline	N06AA09	Metoclopramide	A03FA01
Aripiprazole	N05AX12	Mianserin	N06AX03
Amantadine	N04BB01	Mirtazapine	N06AX11
Benztropine	NO4AC01	Moclobemide	N06AG02
Benzhexol	N04AA01	Morphine	NO2AA01
Biperidin	N04AA02	Nitrazepam	N05CD02
Buprenorphine	N02AE01	Nortryptyline	N06AA10
Buspirone	N05BE01	Olanzapine	N05AH03
Carbamazepine	N03AF01	Orphenadrine	N04AB02
Cetirizine	R06AE07	Oxazepam	N05BA04
Chlorpheniramine	R06AB05	Oxybutynin	G04BD04
Chlorpromazine	N05AA01	Oxycodone	N02AA05
Citalopram	N06AB04	Paroxetine	N06AB05
Clemastine	D04AA14	Pericyazine	NO5AC01
Clomipramine	N06AA04	Phenobarbital	N03AA02
Clonazepam	N03AE01	Phenytoin	N03AB02
Clonidine	S01EA04	Pizotifen	N02CX01
Codeine	R05DA04	Pramipexole	N04BC05
Cyproheptadine	R06AX02	Prazosin	C02CA01
Darifenacin	G04BD10	Pregabalin	N03AX16
Dexchlorpheniramine	R06AB02	Primidone	N03AA03
Dextromethorphan	N02AC04	Prochlorperazine	N05AB04
Diazepam	N05BA01	Promethazine	R06AD02
Dihydrocodeine	N02AA08	Quetiapine	NO5AH04
Diphenhydramine	D04AA32	Risperidone	N05AX08
Disopyramide	C01BA03	Ropinirole	N04BC04
Doxazosin	C02CA04	Selegiline	N04BD01
Dothiepin	N06AA16	Sertraline	N06AB06
Doxepin	N06AA12	Solifenacin	G04BD08
Escitalopram	N06AB10	Tamsulosin	G04CA02
Fentanyl	N02AB03	Temazepam	N05CD07
Fexofenadine	R06AX26	Terazosin	G04CA03
Flunitrazepam	N05CD03	Tolterodine	G04BD07
Fluoxetine	N06AB03	Tramadol	NO2AX02
Fluphenazine	NO5AB02	Tranylcypromine	N06AF04
Fluvoxamine	N06AB08	Triazolam	N05CD05
Gabapentin	N03AX12	Trifluoperazine	N05AB06
Haloperidol	N05AD01	Trihexyphenidyl	N04AA01
Imipramine	N06AA02	Trimipramine	N06AA06
Lamotrigine	N03AX09	Valproic Acid	N03AG01
Levetiracetam	N03AX14	Venlafaxine	N06AX16
Loperamide	A07DA03	Ziprasidone	N05AE04
Loratadine	R06AX13	Zopiclone	N05CF01
Lorazepam	N05BA06	Zolpidem	N05CF02
Lormetazepam	N05CD06	Zuclopenthixol	N05AF05
Methadone	N07BC02		

After enrolment, participants will be stratified using a frailty index (FI), which will be based on a cumulative deficit model using 15 relevant items common to the interRAI Homecare and Contact assessments. Cut-off values for each stratum will create three equal-sized frailty strata based on New Zealand interRAI HC and CA data used for developing the frailty index. Participants will be stratified into one of three frailty strata (low, medium, high) and allocated in a 1:1 ratio within each strata to the intervention and control arms of the trial.

### Study setting

This trial will be conducted at the University of Otago, Christchurch, in the Canterbury provincial region of New Zealand. Study pharmacists will visit participants in their homes, where they will review medication use at the time of their visit.

### Participants

Participants will be eligible for inclusion if they are as follows:
Are aged ≥65 yearsHave undergone an interRAI Home Care [24] or contact [25] assessmentAre regularly taking at least one anticholinergic or sedative medication as shown in the interRAI or dispensing records.

Participants will be excluded from the study for any of the following reasons:
Not consenting for their interRAI data to be used for researchHaving a psychiatric disorder or dementia disease (e.g., Alzheimer’s disease, dementia, schizophrenia, abnormal thought processes, delusions, hallucinations)Scoring 3 or higher on the interRAI Cognitive Performance ScaleHaving a terminal illness with life expectancy ≤6 monthsDetermined as non-frail by having no deficits in the frailty indexHaving an initial DBI score of <0.5 (DBI score of 0.5 is the equivalent of one DBI medication being taken at the minimum efficacious dose) [14].Having a potentially life-threatening drug interaction requiring urgent medical intervention (during the study period)

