#### Randomization and allocation

Predefined randomization lists with a 1:1 allocation will be calculated by the study’s data manager using a Mersenne Twister algorithm. The algorithm will be repeatedly run until a list is identified that shows a difference in the total number of intervention and control arm participants of not more than three participants at any given point in the process. Centralized allocation is considered neither viable nor required in this community-based study setting, as the participants become available at random through the interRAI assessment process. The randomization list is securely stored on the university’s computer system and not available to any other research team member. Each frailty strata will have its randomization list and set of treatment allocations concealed in sequentially numbered sealed opaque envelopes. Allocations will be made by the study administrator, who will select the next allocation matching a participant’s frailty strata when the participant’s home visit is booked. The envelopes are opened after completion of the pre-intervention medication review. If a participant is discovered to be ineligible during the pre-intervention medication review, the corresponding envelope is returned and used with the next available participant.

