#### Intervention arm

In the intervention arm of the trial, pharmacists will discuss with participants the medical conditions with which the DBI medications have been prescribed and their experiences with these medications. The consultation will determine if the potential harm of DBI medications prescribed outweigh their possible benefits. The participant and their family’s beliefs about the continued need for these medications and their preferences regarding willingness to discontinue these medications will also be determined via the consultation. After the consultation, target anticholinergic/sedative medications will be documented along with the participant’s concerns regarding these medications. Study pharmacists will consider the participants’ medical history as conveyed by the participants, their interRAI assessments, and their electronic medication records, if available.

The deprescribing implementation strategy that will be employed will focus on reducing or stopping anticholinergic and sedative medications to reduce participants’ DBI scores, using a process that was adapted from [2] and previously trialled in a New Zealand residential aged care setting [28, 29]. The process used in this study will differ from that used in the above residential care study because our study pharmacists will not have access to prescribing lists and clinical records before meeting the participants. Nevertheless, face to face consultations with the study pharmacists will capture rich data on participants’ medical history, medication lists, and their beliefs about their medications.

The deprescribing medication review will involve the following:
Pharmacist review of medication useParticipant consultationPharmacists suggesting changes in DBI medications to GPsGP consultation with the participantsGP decision to revise or not to revise DBI medication prescriptions

All medication reviews and DBI calculations will be reviewed and verified independently by a senior pharmacist (author [name]). All suggestions developed on potential deprescribing will be peer-reviewed by another study pharmacist before sending them to the participant’s GP, with additional expertise being available from the senior pharmacist.

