#### Control arm

If allocated to the control arm, the pharmacist will conduct the medication review without discussing deprescribing options with participants. The control group participants will continue to receive routine care from their GP.

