#### Statistical analysis

The data analysis will use the intention-to-treat principle (where all available data, including records showing non-adherence to the protocol, from participants will be included in the analysis). Thus, imputation will not be used for missing data.

We will compare the proportions of the outcome measures using a chi-squared test and present results with a 95% confidence interval.

We will present Kaplan-Meier survival curves for analysis of hospitalizations, emergency department visits, entry into aged residential care, and mortality within subgroups. Subgroups will include control low frailty, control medium frailty, control high frailty, intervention low frailty, intervention medium frailty, and intervention high frailty. The analyses will be controlled for age and sex, with death as a censored event. We will then conduct a competing risk analysis using cumulative incidence functions (CIF). For example, where entry to aged residential care is the primary event of interest, death is the competing event. The CIFs are the probability of observing these events before the end of the 6-month follow-up period.

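### The drug-interaction exclusion has no cut-off at allocation, so as written it allows removal after randomisation, contrary to the stated intention-to-treat analysis

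*Protocol article*

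**What the plan says.** The Participants section introduces its exclusion list with "Participants will be excluded from the study for any of the following reasons". One entry reads "Having a potentially life-threatening drug interaction requiring urgent medical intervention (during the study period". It is the only entry in the list with a time span that runs through the study.

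Under Randomization and allocation, "The envelopes are opened after completion of the pre-intervention medication review". The same section has a rule for ineligibility discovered before that moment: "If a participant is discovered to be ineligible during the pre-intervention medication review, the corresponding envelope is returned and used with the next available participant". It has none for a criterion met once the envelope is open.

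Under Statistical analysis, the principle is intention-to-treat, glossed to mean that "all available data, including records showing non-adherence to the protocol, from participants will be included in the analysis". The next sentence rules out imputation of missing data. The Clinical responsibility section says that the study will not record why people withdraw or drop out, death excepted.

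**The concern.** An eligibility criterion should be settled before allocation. If it can be met afterwards, it becomes a rule for taking randomised people out of the trial, and the arms compared are no longer the arms randomised.

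Two features make this more than a formality. First, the trigger concerns the participant's medicines, and the primary outcome is a change in medicines, so removal may be related to outcome. Second, what happens after allocation differs by arm. The intervention arm has a consultation about its DBI medicines, and "All suggestions developed on potential deprescribing will be peer-reviewed by another study pharmacist before sending them" to the GP, who then consults with the participant. In the control arm, "the pharmacist will conduct the medication review without discussing deprescribing options with participants", and routine care follows. If the extra attention brings more interactions to light, more people could leave one arm than the other. Because reasons for leaving are not recorded, the final report could not show whether this had happened.

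**Working it through.** **Step 1: the passages side by side.**
- Participants: meeting the criterion means exclusion from the study, not just from the intervention, and the bracketed time span does not stop at allocation.
- Randomization and allocation: the return-the-envelope rule covers only the pre-intervention review.
- Outcomes: five ways of finishing the trial are listed. Exclusion by the study team after allocation is not among them and could fall only in the last category, withdrawal or other loss.
- Primary outcome: ΔDBI needs a 6-month (T2) value. Someone removed before T2 has none, and without imputation leaves the primary comparison.

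The conflict with intention-to-treat follows from these passages alone. It does not depend on whether removals differ by arm.

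**Step 2: reproduce the plan's sample size.** Inputs from Power and sample size: 4% in control and 14% in intervention with ΔDBI ≥ 0.5, α = 0.05, power 90%. Sidedness is not stated; two-sided is assumed. With unpooled variance:

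n = (1.960 + 1.282)² × (0.04×0.96 + 0.14×0.86) / 0.10² = 166.9, so 167 per arm, as stated.

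The exact power of the uncorrected chi-squared test with 167 per arm at 4% and 14% is 91.4%.

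**Step 3: what removals could do.** The documents give no interaction rate, so the number removed, k, is an assumption. Expected intervention responders are 0.14 × 167 = 23.38. All k are taken from the intervention arm; the control arm stays at 167 and 4%. Three assumptions about who is removed:
- all responders: rate = (23.38 − k)/(167 − k)
- same mix as the arm: rate stays at 14%
- all non-responders: rate = 23.38/(167 − k)

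| k (share of arm) | All responders: rate, power | Typical of arm: power | All non-responders: rate, power |
|---|---|---|---|
| 0 | 14.0%, 91.4% | 91.4% | 14.0%, 91.4% |
| 3 (1.8%) | 12.4%, 82.5% | 91.3% | 14.3%, 92.3% |
| 5 (3.0%) | 11.3%, 72.2% | 90.6% | 14.4%, 92.4% |

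The loss of numbers is trivial in itself. Only selective loss of responders matters, and a few people then suffice because only about 23 responders are expected in that arm.

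**The case against.** **The conflict may be one of wording only.** The criterion sits in an eligibility list and nowhere says that collected data are discarded. The analysis section keeps all available data, even from people who departed from the protocol. The Blinding section provides for unblinding when a health concern needs immediate attention, so urgent problems have a route other than removal. The flowchart and the full protocol are not visible here and may say more. This has weight, but keeping the data already collected does not supply a missing T2 value, and nothing in the article says that such a person stays in follow-up.

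**A reader might infer that interactions will be found more often in the intervention arm.** The document does not say so. The main point of detection is the in-person review common to both arms, completed before the envelope is opened, where exclusion does no harm to intention-to-treat. The follow-up review uses the same process in both arms, with a different, blinded pharmacist. Senior-pharmacist verification covers all medication reviews. The peer review specific to the intervention arm concerns deprescribing suggestions and is not described as an interaction check, and electronic medication records are considered only if available. The post-allocation consultation and GP contact do differ, so unequal detection is possible but not established.

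**A reader might infer that every other exclusion is settled before allocation.** That is not secure either. Under Data entry and quality checks, DBI calculations are verified and corrected after the visit, so an initial DBI below 0.5 could also come to light once the envelope is open. What sets the interaction criterion apart is its stated time span.

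**A reader might infer that the trial stands to lose 9 to 19 points of power.** Those losses require everyone removed to be an intervention-arm responder. The criterion is not limited to DBI medicines, so nothing in the text makes that likely.

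**Conclusion.** The point holds as a contradiction to be reconciled. As worded, the criterion permits exclusion of randomised participants for a later event, and the primary analysis would then omit them without a recorded reason. That is inconsistent with the intention-to-treat statement whatever the arm.

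The document does not support a claim of demonstrated bias. Unequal removal by arm is an inference, and with no rate given neither its size nor its direction can be derived. Under the plan's own inputs, a two-sided test and 3 to 5 removals from the intervention arm only, power ranges from 72% (five removed, all responders) to 92% (all non-responders), against 91% with none removed. In the worst case the error is towards missing a real effect. The change is worth making because the rule concerns prescribing, as the outcome does, and is easily corrected.

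**What to change.** Reconcile the Participants and Statistical analysis sections:

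1. As an eligibility rule, limit the criterion to interactions identified before the allocation envelope is opened, and delete the bracketed time span.
2. State that anyone in whom an interaction is found later stays in T2 and linked-registry follow-up and is analysed in the allocated arm.
3. Record these events and report them by arm.

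Clinical handling of an interaction stays with the GP, as the Clinical responsibility section says, and is not addressed here.

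The cost is a short amendment through the review route described under Ethics and protocol changes, recording of these events (the protocol now records no reason for leaving other than death) and continued follow-up of the people concerned. No sample-size input changes. The Trial status section shows the trial already under way, so new wording would not undo exclusions already made; any such exclusions should be listed by arm.
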